### Concurrent therapy

All participants will be maintained on the same medications throughout the entire study period, as medically feasible, with no introduction of new chronic therapies. Data will not be analyzed from participants who make changes to the type of treatment they are receiving during the 10-week study period. However, data from participants who change the dose of their medication, without changing the type, will be analyzed. Standard therapy (for example, medications and psychotherapy) for schizophrenia is allowed, except for any other cognitive training games.

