**Fig. 1 Fig1:**
[figure not shown]
Participant flow through study. This figure illustrates participant enrollment, allocation, and follow-up throughout the study

All participants who meet the inclusion criteria will be randomly assigned to one of three conditions: (1) a working memory-training condition (27 participants), (2) a processing speed-training condition (27 participants), or (3) a no-training control condition (27 participants). Participants in the two training conditions will be blind to the fact that there are multiple training groups and to which cognitive domain they have been assigned to (that is, no mention of “working memory” or “processing speed” will be made). Group assignment will be determined by a Microsoft Excel randomization generator (that is, computer-generated random numbers). The random allocation sequence will be generated by a trained research assistant. Randomization will be performed as complete randomization with a 1:1:1 allocation. The allocation sequence will be concealed in sealed envelopes until the end of the pre-training assessment. A trained research assistant will also assign participants to interventions. Participants who are randomly assigned to the no training control condition will be given the opportunity to access the cognitive training games after their post-assessments. All researchers administering pre- and post-assessments will be blind to the group assignments of each participant.

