### Procedure

In the first session, following informed consent (consent form provided in Additional file 3), demographic information will be collected and the Vocabulary and Matrix Reasoning subtests of the WASI-II will be administered by trained graduate students. Next, the trained students will interview participants with the SCID-5. Finally, the PANSS will be administered. The entire first session should last approximately 3 hours and 35 minutes.

The second session will include pre-assessment of all neurocognitive, social cognitive, and functioning measures described above. This session will be approximately 2 hours and 45 minutes in duration. To reduce the impact of fatigue and carryover effects on the results, the administration order of all cognitive and functional measures will be counter-balanced using a Williams Design Latin Square [104]. Testing will be administered by trained graduate students and research assistants, who will be blind to the randomization until completion of the baseline assessment. Blinding will only be broken if knowledge of the patient’s treatment group is necessary for further patient management. Following the baseline assessment, participants will be randomized and provided with training instructions, including how to access the online training in addition to the training schedule. Training program names (for example, *Bubble Math*, *Moving Memory*) will not be concealed; however, participants will not be informed of the objectives or hypotheses of the current study, and will be unaware of the other training conditions. Participants will be contacted half way through training (after approximately 5 weeks) to complete the mid-point motivation questionnaire.

The 3 hour 30 minute post-training assessment will be composed of the same measures (that is, neurocognitive measures, social cognitive measures, and measures of functional status) described above and using parallel forms where indicated, in addition to a re-administration of the PANSS. All post-assessments will be conducted by trained graduate students and research assistants who are blind to the randomization of each participant. All assessment materials will be scripted to ensure consistency across examiners and across assessments.

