### Data sets analyzed

All eligible participants who are randomized into the study and complete at least 50 % of the cognitive training will be included in the completer analysis, following similar cut-offs in prior cognitive training research [Lawlor-Savage L, Goghari VM: Dual n-back working memory training in healthy adults: a randomized comparison to processing speed training, submitted]. All eligible participants who are randomized into the study will be included in the intent-to-treat analysis. Data collection will stop when the goal sample size has been reached or when new participants are unable to be recruited for a significant period.

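### Excluding randomized patients who change treatment type contradicts the intent-to-treat set, and the completer set has no rule that controls could meet

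*Protocol article*

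**What the plan says.** Concurrent therapy asks that participants be "maintained on the same medications throughout the entire study period, as medically feasible", so it foresees that some will have to change. It then fixes who is analysed: "Data will not be analyzed from participants who make changes to the type of treatment they are receiving during the 10-week study period". The next sentence sets the contrasting case: "data from participants who change the dose of their medication, without changing the type, will be analyzed".

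Data sets analyzed defines two sets. The first covers randomized, eligible participants who "complete at least 50 % of the cognitive training will be included in the completer analysis". The second is stated without exception: "All eligible participants who are randomized into the study will be included in the intent-to-treat analysis".

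Two facts on timing matter. The Procedure section says: "Following the baseline assessment, participants will be randomized and provided with training instructions". And the text below the flow chart, under Recruitment process and study population, says that controls "will be given the opportunity to access the cognitive training games after their post-assessments". Study design agrees: controls are offered training only once the 10-week wait is over.

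**The concern.** A patient who changes treatment type in, say, week 6 is removed from analysis by one section and kept in the intent-to-treat analysis by another. Whoever analyses the trial could follow either rule and cite the protocol for it, even after seeing the data.

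The choice matters because the change happens after randomization. Excluding people for it gives up the protection that randomization provides, and the rule as worded reaches every primary outcome (working memory, processing speed, fluid intelligence). If changing treatment is related to how a patient is doing, or is more common in one arm, the arms that remain are no longer comparable.

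The completer set has a related problem. Its entry condition is an amount of training done, but one of the three arms has no training to do before the outcome is measured.

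**Working it through.** The contradiction is textual, and the plan gives no figure on this point to reproduce. The check is to see whether any reading lets both statements stand.

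1. **Is the exclusion made after randomization?** Yes. Randomization follows the baseline assessment, and the rule covers the 10 weeks after it.
2. **Does the word eligible reconcile the two?** No. The inclusion and exclusion criteria under Recruitment process and study population do not mention treatment change during the study, and they are settled before allocation.
3. **Is the exclusion limited to one analysis set?** Not in the text. It is worded as a general rule on whose data are analysed, and the sentence on dose changes continues in the same general terms. Limiting it to the completer set would remove the conflict, but the article does not say so.
4. **Can a control meet the completer condition?** Not before post-assessment. Either no control enters the set, or controls enter without any filter while trainees are filtered on adherence. The second reading is the sensible one, but it is an inference, because the article gives no rule for controls.

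**Illustration of size.** The article gives no rate of treatment change, no adherence rate and no correlation. Every input below is an assumption, except the 27 participants per arm and d = 0.70, which are in Recruitment process and study population.

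*Treatment-change exclusion.* Shift in the contrast = (excess proportion excluded in one arm) × (mean difference in SD between excluded and retained patients).
- 0.05 × 0.5 = 0.025, about 0.03 SD
- 0.15 × 1.0 = 0.15 SD

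With 27 per arm, that excess is 27 × 0.05 = 1.4 to 27 × 0.15 = 4.1 patients. The sign depends on which arm loses more. With equal proportions and equal differences in all arms, the shift is zero.

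*Completer filter, if applied to the trained arms only.* Let q be the fraction filtered out, c the q-quantile of the standard normal, φ its density, and r the correlation of adherence with the analysed change score. Shift = r × φ(c) / (1 − q).
- q = 0.20: φ(c)/(1 − q) = 0.280/0.80 = 0.350. For r = 0.2, 0.3, 0.4 the shift is 0.07, 0.105, 0.14 SD.
- q = 0.40: φ(c)/(1 − q) = 0.386/0.60 = 0.644. For r = 0.2, 0.3, 0.4 the shift is 0.13, 0.19, 0.26 SD.

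Against the planned d of 0.70, these run from 0.07/0.70 = 10 % to 0.258/0.70 = 37 %. The upper end takes both assumptions at their extreme. The formula takes r as positive; a negative r reverses the sign.

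**The case against.** The strongest reply is that an intent-to-treat analysis is planned, and that a completer analysis beside it is common and legitimate. The article never says that conclusions rest on completers. That stands: the completer set is not an error in itself, and its fault is limited to the missing rule for controls and the need to label it as non-randomized.

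A second reply is that the treatment-change rule applies to all arms alike, so it biases only if changes relate to arm or outcome. That also stands, and it is why no size or direction is claimed. It does not remove the contradiction.

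Three stronger readings are tempting, and the article does not support them.
- A reader might infer that the completer contrast favours training on every primary outcome, because adherent patients function better. But the Statistical analysis section tests group by time and training-related gains, so a stable difference in level largely cancels and only a link between adherence and change matters. The Background suggests that people with slower initial speed gain most and that high baseline ability may limit gains, so adherent trainees could gain less. Weekly monitoring with phone reminders may also limit non-adherence.
- A reader might infer that the repeated measures ANOVA discards anyone without a post-training score. The article states no missing-data rule, and that detail may sit in an analysis plan that is not shown.
- A reader might infer a definite loss of power from the exclusions. Without a rate of treatment change, no such figure can be supported, and some of these patients may already be lost through the withdrawal provision for worsening symptoms.

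**Conclusion.** The point holds in a limited form. The two sections conflict for any randomized participant who changes treatment type, and no wording in the article resolves this. It rests on the text alone and needs no assumption. If the exclusion is applied as written, it is a post-randomization exclusion that can bias any primary comparison. How much, and in which direction, cannot be known from the article. The 0.03 to 0.15 SD range is an illustration under assumed rates, not an estimate.

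The completer set is not a randomized comparison under either reading of how controls enter. The 0.07 to 0.26 SD range applies only if controls are unfiltered and the assumed adherence and correlation hold. Because the completer analysis stands beside an intent-to-treat analysis, this is a matter of definition and labelling.

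**What to change.** Reword two paragraphs.

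- **Data sets analyzed:** name the intent-to-treat analysis as primary, with all randomized participants analysed in the arm to which they were allocated.
- **Concurrent therapy:** say that a change in type of treatment is recorded but is not a reason for exclusion from the intent-to-treat set. Confine the exclusion to a labelled sensitivity analysis. This concerns only whose data are analysed; what the section says about keeping medication constant is unaffected.
- **Completer analysis:** call it supportive and non-randomized, and state the rule by which controls enter it.

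The cost is a few sentences and one sensitivity analysis. The downside is slight dilution of the effect by treatment changers and non-adherent patients. Trial status says that recruitment had not begun, so at that point the change could be made before any data existed.

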### Ethics, consent, and permissions

This study has been reviewed and approved by the Conjoint Health Research Ethics Board (CHREB) at the University of Calgary (study ID number: REB15-0526). The study has been registered by ClinicalTrials.gov (registration number: NCT02478827). All participants will receive verbal and written information regarding the study procedures, and all participants must provide written informed consent before inclusion in the study. This will be completed by graduate students and/or trained research assistants. Any protocol amendments will be reported immediately to the ethics board and will be discussed in the final manuscript. All data will be kept in password protected digital files with individual names removed to ensure confidentiality.

### Discontinuation of participants

Participants will be discontinued from the study if they withdraw their consent. Participants may be withdrawn from the study if they experience a significant increase in schizophrenia symptoms.

### Training programs

Processing speed and working memory-training programs will be provided by BrainGymmer [83] and accessed online. BrainGymmer was chosen over other training programs due to its interesting and engaging user interface, engaging exercises, and flexibility in game design (that is, games were easily adapted to incorporate researcher ideas). Moreover, the BrainGymmer program is relatively inexpensive compared to other programs and therefore may be affordable for this population.

All participants will be instructed to train for 30 minutes per day, 5 days per week, for a total of 10 weeks in a comfortable location of their choice (for example, home computer). This time frame (that is, 25 hours of training) was chosen based on research indicating that trained skills improved substantially during the first 20 to 25 hours of cognitive training and only minimally thereafter in individuals at high risk for psychosis [84]. Each training program will consist of three exercises (described below), and participants will be instructed to distribute their time approximately equally across the three exercises. Notably, all exercises are adapted to individual performance, such that the difficulty level is increased if the individual’s performance is above the threshold for their current level, and difficulty level is decreased if the individual’s performance falls below the minimum performance required at the current level. Difficulty thresholds on BrainGymmer were determined based on internal play testing, test panel feedback (with members from over 20 different countries), user feedback, and game result data. Training compliance will be monitored through weekly electronic data upload, and participants will receive phone call reminders if compliance is low (that is, below 50 % of the required training for the week).

#### Working memory training

Participants who are randomly assigned to receive working memory training will be instructed to access the following three games: *N Back*, *Multi Memory*, and *Moving Memory*. All three exercises incorporate both maintenance and manipulation aspects of working memory. Examples of these exercises can be seen in Additional file 1.

In *N Back*, cards with various shapes and colors appear on the screen and participants are asked to remember the shapes and colors. The goal of the exercise is to determine whether the current card matches with the card that was shown *n*-back cards before the current one. The difficulty level is increased by increasing the number of cards between the current stimulus and the one it is being compared to (that is, the “*n*”).

In *Multi Memory*, tiles appear in a grid and participants are asked to remember the shape, color, and position of the tiles to try to reproduce them after the display disappears. The level of difficulty is increased by increasing the number of tiles, the size of the grid, the number of different shapes, and the length of time the user is given to look at the tiles.

Finally, in *Moving Memory*, tiles with colored shapes appear on the screen, and each tile has a unique number written below. Participants are required to remember the numbers associated with each colored shape to allow them to choose a pair of numbers later that are associated with matching shapes. Each time a correct matching pair is identified, the tiles move to new positions, thus requiring participants to use the numbers, rather than spatial locations, to correctly match shape-pairs. Difficulty level is increased by increasing the number of card pairs to be matched, increasing the number of background colors, shapes, and shape colors, and by decreasing the amount of time the display is shown.

#### Processing speed training

Participants who are randomly assigned to receive processing speed training will be instructed to access the following three games: *Line It Up*, *Sliding Search*, and *Bubble Math*. All three exercises require timely information processing and have a minimal memory component. Examples of these exercises can be seen in Additional file 2.

In *Line It Up*, colored tiles with different shapes appear on the screen in a horizontal line (that is, reference line). Participants are required to order a shorter line of colored tiles (that is, target line) using the first line as a reference as quickly as possible. The target line contains only a portion of the tiles present in the reference line. Difficulty level is increased by increasing the lengths of the target and reference lines, with shapes and colors that begin to look very similar.

In *Sliding Search*, a grid of several reference images is presented at the top of the screen, and participants are required to choose which image matches the image shown at the bottom of the screen as quickly as possible. Difficulty is increased by increasing the speed at which the image is moved across the bottom of the screen (that is, requiring faster responding), as well as changing the reference grid to include more similar, nuanced images.

In *Bubble Math*, participants are asked to complete simple math equations, which are moving across the screen, as quickly as possible. Difficulty is increased by increasing the number of questions asked per minute as well as the range of numbers used in the problems.

### Outcome measures

#### Baseline measures

At baseline, participants will complete a form assessing demographic factors (sex, age, ethnicity, income, education, and maternal and paternal education). Next, the Vocabulary and Matrix Reasoning subtests of the WASI-II [85] will be used to estimate the IQ of all participants. Participants will then go through the SCID-5 for DSM-5 semi-structured interview. Finally, the Positive and Negative Syndrome Scale (PANSS) [86] will be used to assess symptom severity in all participants.

#### Pre-training and post-training measures

The following neurocognitive, social cognitive, and functional status measures will be administered prior to randomization into training, as well as immediately post-training. The entire battery will be approximately 2 to 4 hours in duration at each sitting (see Table 1).

**Table 1 Tab1:** List of all tasks and measures

Task	Cognitive domain	Primary or secondary outcome	Transfer hypothesis (WM)	Transfer hypothesis (PS)	Pre-test time	Post-test time
Demographic information form	N/A	N/A	N/A	N/A	10 minutes	N/A
WASI-II Vocabulary	Crystallized intelligence	N/A	N/A	N/A	15 minutes	N/A
WASI-II Matrix Reasoning	Fluid intelligence	N/A	N/A	N/A		
SCID-5-RV for DSM-5	N/A	N/A	N/A	N/A	2 h 30 min	N/A
PANSS	N/A	Secondary	N/A	N/A	40 minutes	40 minutes
Session 1 total:					3 h 35 min	
Neurocognition measures:						
N-Back Task	Working memory (visual)	Primary	Near	Far	15 minutes	15 minutes
WAIS-IV Digit Span	Working memory (auditory)	Primary	Near	Far	5 minutes	5 minutes
Maintenance and manipulation (computer)	Working memory (visual-spatial)	Primary	Near	Far	15 minutes	15 minutes
WAIS-IV Symbol Search	Processing speed	Primary	Far	Near	5 minutes	5 minutes
D-KEFS Color Naming	Processing speed	Primary	Far	Near	N/A	N/A
D-KEFS Color-Word Interference Test	EF: Inhibition, set-shifting	Secondary	Far	Far	5 minutes	5 minutes
D-KEFS Trail Making Test	EF: Cognitive flexibility	Secondary	Far	Far	5 minutes	5 minutes
Raven’s Standard Progressive Matrices	Fluid intelligence	Primary	Far	Far	25 minutes	25 minutes
Cattell’s Culture Fair Test	Fluid intelligence	Primary	Far	Far	15 minutes	15 minutes
Social cognition measures:						
Geneva Emotion Recognition Test	Emotion recognition	Secondary	Far	Far	20 minutes	20 minutes
Hinting task	Theory of mind	Secondary	Far	Far	10 minutes	10 minutes
Beliefs regarding cognition measures:						
Need for Cognition Scale	N/A	Secondary	Far	Far	10 minutes	10 minutes
Theories of Intelligence Scale	N/A	Secondary	Far	Far	5 minutes	5 minutes
Daily functioning measures:						
Cognitive Failures Questionnaire	N/A	Secondary	Far	Far	5 minutes	5 minutes
UPSA-Brief	N/A	Secondary	Far	Far	15 minutes	15 minutes
SOFAS	N/A	Secondary	Far	Far	N/A	N/A
Questionnaires:						
Brief Sleep Questionnaire	N/A	N/A	N/A	N/A	5 minutes	5 minutes
Motivation Form	N/A	N/A	N/A	N/A	5 minutes	5 minutes
Pre- and post-test total:					2 hr 45 min	3 hr 30 min

#### Neurocognitive measures

Neurocognitive measures will examine working memory, processing speed, executive functions, and fluid intelligence.

##### Working memory - N-Back task

A participant’s ability to maintain, monitor, and manipulate information will be assessed with an N-Back task. In this task, participants will view a set of visually presented random shapes and will indicate whether each stimulus matches the stimulus that appeared *n* trials previously (2-, 3-, or 4-back). This task has been used as a measure of working memory in previous studies [33]. This task will be used as a near-transfer measure of working memory.

##### Working memory - Digit Span Task

Auditory working memory abilities will be assessed using the Digit Span subtest of the Wechsler Adult Intelligence Scale 4^th^ Edition (WAIS-IV) [65]. In this task, participants will first be required to repeat verbally presented digits in the same order that they were presented (digits forward), then in reverse order (digits backwards), and finally in numerical order (digits sequencing). Digit Span is one of the most widely used measures of working memory, and assesses both maintenance and manipulation aspects of working memory [87].

##### Working memory - Spatial Maintenance and Manipulation Task

Visuospatial working memory will be assessed using the computerized Spatial Maintenance and Manipulation task [88]. In the spatial maintenance condition, participants are asked to remember the positions of circles on the screen after a short delay. In the maintenance and manipulation condition, participants are asked to mentally rotate the positions of the circles across a horizontal plane and remember the new position of the circles. This talk allows for an examination of the different components of working memory, with the maintenance condition assessing short-term memory and the manipulation condition examining also the executive aspects of working memory.

